### Data Management and Analysis

#### Overview

ODK data will be downloaded into Microsoft Excel and transferred to Stata 14 (StataCorp LLC) for cleaning and analysis. The primary analytical approach will follow the intention-to-treat principle, with participants in the intervention arm considered exposed to the intervention regardless of whether they received specific intervention services. We will assess for any contamination by conducting and comparing the results of the intention-to-treat and per-protocol analyses. Descriptive statistics (means, medians, and proportions) will be used to describe participant characteristics across the study arms. We will control for characteristics that are not balanced across the study arms in the fitted regression models. Chi-square tests will be performed for categorical outcomes. Log-binomial regression models using generalized linear modeling will be applied to assess associations between each intervention and the outcomes. A *P* value <.05 will be considered statistically significant.

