#### SMS Reminders Only

Participants in this arm will receive up to 3 SMS reminders. The first reminder will be sent on day 0, the day of study enrollment. The second reminder will be sent once the patient’s results are ready. If the patient does not return to complete the TB diagnostic process (ie, testing and receiving results) within 1 day of the second reminder, a third reminder will be sent. This third reminder will serve as a reinforcement, reminding participants to return and complete diagnosis or initiate treatment if they have not already done so. Standardized SMS reminders will be manually sent by the research team through the telecom service providers MTN and Airtel in either Luganda (the local language) or English, based on the participant’s language preference determined at enrollment. The SMS reminders are planned to be 1-way (unidirectional) and the content neutral, excluding any mention of the word “TB” or the patient’s name. The specific wording of the SMS reminders will be co-designed with stakeholders including persons with presumed TB and health workers. Quality control officers will verify the SMS reminders sent daily, checking for the correctness of recipient telephone numbers and ensuring that all reminders are sent on time as per the study procedures. Each day, quality control officers will randomly select at least 4 participants from the SMS reminder arm or from among those scheduled to receive the second or third reminder and cross-check their details on the study telephone to confirm that the participant received the appropriate SMS reminder and in the preferred language. They will also cross-check the correctness of the telephone number that received the SMS reminder vis-à-vis the one recorded in the register for persons with presumed TB. Successful transmission of reminders will be checked by requesting sample statements from the telecom companies to confirm SMS dispatch to patients. Moreover, at follow-up, participants will be asked whether they received either an SMS reminder or a telephone call and a transport incentive, further corroborating whether the participant received the SMS reminder.

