#### SMS Reminders and a Transport Incentive

Participants in this arm will receive the same SMS reminder package as those in the SMS reminder–only arm, along with a transport incentive of UGX 10,000 (approximately US $3). This transport incentive will be provided either after submitting a sputum sample in case the participant was unable to produce the sputum on the first day of the health facility visit or upon receiving their test results. The transport incentive will be disbursed through a prepaid mobile money system to ensure accountability for both the patient and the study team and to comply with the ongoing government campaign promoting the use of electronic cash [35]. These interventions will be administered in addition to the SOC provided at the health facility.

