#### Telephone Calls and a Transport Incentive

The same telephone call package received by participants in the telephone call–only arm will be offered to those in this arm, along with a transport incentive of UGX 10,000 (approximately US$ 3). This will be in addition to the SOC received at the health facility. This transport incentive will be provided either after submitting a sputum sample in case a participant was unable to produce sputum on the first day of the hospital visit or upon receiving their test results. We will use the prepaid mobile money system to pay the transport incentive to participants in this study arm.

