### Trial End Points, Outcomes, and Timelines

The primary end point for the trial is completion of the TB diagnosis process within 30 days of being recruited. Completion of TB diagnosis will be defined as submitting a sputum sample for Xpert MTB/RIF testing and receiving test results within 30 days of being identified as a person with presumed TB. The 30-day follow-up period was selected based on previous studies for comparison [25,33]. Completion of TB diagnosis will be measured as the proportion of patients who completed TB diagnosis within 30 days out of all persons with presumed TB recruited into the study.

The secondary outcomes will include (1) TB treatment initiation, which will be defined as starting TB treatment within 30 days of being diagnosed (this will be measured as the proportion of patients diagnosed with TB who initiated treatment out of the total number of patients diagnosed with TB recruited into the study); (2) median turnaround times for TB diagnosis and treatment initiation; and (3) acceptability and feasibility of the study interventions. The detailed procedures and timelines are indicated in Table 1.

**Table 1. T1:** Study procedures and timelines.

Study procedure	Screening	Baseline	Day 0	Results available	Day after results reminder	Day 30
Enrollment						
Eligibility screening	✔					
Informed consent	✔					
Allocation	✔					
Sociodemographic information		✔				
Clinical history		✔				
Knowledge of and attitudes regarding TB^a^		✔				
Interventions						
SMS reminders			✔	✔	✔	
Telephone calls			✔	✔	✔	
Transport incentives				✔		
Assessments						
Sputum submission						✔
Receipt of results						✔
Receipt of interventions						✔
Treatment initiation for those diagnosed						✔
Acceptability assessment						✔
Qualitative study on perceptions and experiences of the interventions						✔

a TB: tuberculosis.

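### Comparing intention-to-treat with per-protocol results does not isolate contamination, and a per-protocol set based on services received would select on progress to the primary endpoint

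*Protocol article*

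**What the plan says.** The Overview under Data Management and Analysis makes intention-to-treat primary, with intervention participants "considered exposed to the intervention regardless of whether they received specific intervention services". It then fixes the contamination check: "We will assess for any contamination by conducting and comparing the results of the intention-to-treat and per-protocol analyses". The article does not say who enters the per-protocol set.

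The primary endpoint (Trial End Points, Outcomes, and Timelines) is "submitting a sputum sample for Xpert MTB/RIF testing and receiving test results within 30 days of being identified as a person with presumed TB".

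Whether a participant receives a component depends on how far they have got:

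- **Incentive, SMS arm:** one payment trigger reads "This transport incentive will be provided either after submitting a sputum sample in case the participant was unable to produce the sputum" at the initial visit; the other is collection of the result. The call arm has the same rule: after submission if the participant could not "produce sputum on the first day of the hospital visit or upon receiving their test results". Table 1 marks the incentive only in the column for results being available.
- **Reminder 1 (SMS or call):** sent on day 0 to everyone in the arm.
- **Reminder 2:** sent when results are ready, so sputum must already have been submitted.
- **Reminder 3:** "If the patient does not return to complete the TB diagnostic process (ie, testing and receiving results) within 1 day of the second reminder". The call arms have the same one-day rule.

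Reminders are described as up to three. SOC already includes irregular calls to patients who test positive. Receipt of interventions is assessed at day 30 (Table 1).

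**The concern.** There are two separate problems.

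First, the comparison is the wrong instrument. It can produce a gap when there is no contamination, because removing intervention participants who did not receive a service changes who is compared. It can also miss contamination. If the set is defined only by receipt in the intervention arms, both analyses keep the same SOC group, and any study reminders reaching that group leave no trace in the gap.

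Second, on the natural reading, the incentive is received only after one or both parts of the endpoint have been met. Restricting to recipients drops many of the failures from the incentive arms and none from SOC. A null or modest intention-to-treat result beside a large per-protocol one could then be reported as an effective incentive diluted by contamination, when the difference is an artefact of selection.

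**Working it through.** **Inputs from the protocol.** Prediagnosis loss is 24% in SOC, 14.4% with a reminder alone and 12% with reminder plus incentive (Objectives and Hypothesis). These follow from the stated reductions: 24% × 0.60 = 14.4% and 24% × 0.50 = 12%. As completion they are 76%, 85.6% and 88%, so the design risk ratios are 0.856/0.76 = 1.126 and 0.88/0.76 = 1.158. The 24% and 14.4% are the rates behind the sample size: with the protocol's own Z of 2.238 and 80% power, the pooled two-proportion formula gives 318.0 per full arm. The ratio 2:2:2:1:1 equals four full arms, so 318.0 × 1.5/0.80 × 4 = 2385, against the stated 2389.

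**Assumptions not in the protocol.**
- s, share of non-completers who never submit sputum: 0 to 1.
- u, share of non-completing submitters who could not produce sputum on day 1 and so are paid on submission: 0.30 (single value; varied in step 2).
- r, share of completers who return within one day of reminder 2: 0.30 or 0.60.
- d, probability that a due incentive is paid: 0.90 to 1.00.
- Results become ready for everyone who submits.

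**Set-up.** No intervention works, and completion is 0.76 in every arm. The intention-to-treat risk ratio is 1.00. Each per-protocol set is compared with all of SOC.

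1. *Incentive received, paid on results only.* Every recipient has completed. RR = 1/0.76 = 1.32; difference 100 − 76 = 24 points.

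2. *Incentive received under either trigger.* Completion among recipients = 0.76/[0.76 + 0.24(1−s)u], so RR = 1/[0.76 + 0.24(1−s)u]; d cancels.
   - s = 0: 1/(0.76 + 0.072) = 1.20 (91.3% against 76%, 15 points)
   - s = 0.5: 1/(0.76 + 0.036) = 1.26
   - s = 1: 1/0.76 = 1.32

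   *Dependence on u.* The artefact equals the design value of 1.158 when 0.76 + 0.24q = 0.76/0.88 = 0.8636, where q = (1−s)u is the share of non-completers already paid on submission. That gives q = 0.43. Below it the artefact exceeds the design effect. At q = 1 it vanishes.

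3. *Reminder 2 received.* RR = 1/[0.76 + 0.24(1−s)]: 1.00 at s = 0, 1.14 at s = 0.5, 1.32 at s = 1.

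4. *All three reminders received.* Completion = 0.76(1−r)/[0.76(1−r) + 0.24(1−s)].
   - s = 0, r = 0.60: 0.304/0.544 = 0.559, RR about 0.73
   - s = 0.5, r = 0.60: 0.304/0.424 = 0.717, RR 0.94
   - s = 0.5, r = 0.30: 0.532/0.652 = 0.816, RR 1.07
   - s = 1: RR 1.32

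5. *Received what was due.* Only participants with a due but unpaid incentive are removed. Completion = 0.76d/{0.76d + 0.24[1 − (1−d)(1−s)u]}.
   - d = 1: RR 1.00
   - d = 0.90, s = 0: 0.684/0.9168 = 0.746, RR 0.98
   - d = 0.90, s = 1: 0.684/0.924 = 0.740, RR 0.97

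Simulated trials of the planned size (597 per full arm, 299 per incentive arm) give the same ranges, with intention-to-treat at about 1.00.

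**The case against.** The strongest reply is that the article leaves per-protocol undefined, and that such a definition may properly sit in an analysis plan not shown here. Because reminders are up to three and the incentive falls due only at set steps, a participant who never returns and is never paid has still been handled according to protocol. A set defined as having received what was due is nearly unbiased (0.97 to 1.00 above). This stands. A reader might infer that the per-protocol result is circular whatever definition is used; the documents do not support that.

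The triggers are also not the endpoint itself. The incentive can follow submission alone, and reminder 3 follows one day without return, not a missed 30-day endpoint. So it would be wrong to infer that selecting on all three reminders must bias downward: those recipients have been tested, which pushes the other way. Nor is the day-0 reminder the only component that can precede completion, since later reminders and a submission-triggered incentive can too.

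Finally, if SOC participants who received study services were excluded, the gap would respond to contamination. It would do so only indirectly, still mixed with non-delivery and selection. This reply therefore weakens the point about selection but does not rescue the comparison as the chosen measure of contamination.

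**Conclusion.** The concern holds in two parts of different strength.

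- **Regardless of definition:** the gap between the two analyses does not isolate contamination and is at best an indirect signal of it.
- **Only if per-protocol means services received:** a set restricted to incentive recipients would show RR 1.20 to 1.32 under no effect, against a design RR of 1.158. The upper end is 24 points, twice the 12-point target. The lower end assumes that 30% of non-completing submitters are paid on submission. The artefact stays above the design effect as long as fewer than about 43% of non-completers have been paid. Sets based on later reminders range from 0.73 to 1.32.

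The problem is strongest in the two incentive arms. A reader might infer that the main result is compromised. It is not, because the primary analysis is by intention to treat and does not condition on receipt. What is at risk is the interpretation of a supportive analysis and of any statement about contamination.

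**What to change.** Replace the comparison as the contamination check with a table by arm, including SOC, of study SMS, study calls and transport incentives received, from the day-30 receipt-of-interventions data. Two things must be kept apart from study exposure: the irregular calls that belong to SOC, and the UGX 10,000 compensation paid to every participant at each data collection (Ethical Considerations), which equals the incentive in amount and is easily confused with it. Telecom statements and daily quality checks are described only as samples, so they can corroborate the table but not supply it.

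If a per-protocol analysis is kept as supportive, define it by delivery of what was due at each step and by absence of crossover, not by receipt of the incentive or of later reminders. Report the number of due but undelivered components, since these cause the small remaining bias. An instrumental-variable estimate with day-0 delivery as the exposure is not a substitute: arm also acts through later reminders and, in two arms, the incentive, so the exclusion restriction fails.

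The cost is a change of wording and one extra table from data already planned, limited by self-report and by missing day-30 interviews. A receipt-based per-protocol estimate is no longer reported. With 2355 participants recruited by 28 August 2025 and preliminary analyses under way, the change should be made before any per-protocol result is interpreted.

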### Randomization and Blinding

Eligible participants will be randomly assigned by research assistants to 1 of the 5 study arms using permuted block randomization in a ratio of 2:2:2:1:1 via a predesigned mobile app (Figure 2). The block sizes will be varied to minimize predictability. A computer algorithm will be designed by the biostatistician together with the app designer to generate the allocation sequence in blocks of 8 and 16, assigning their order randomly. The allocation sequence will then be input into the predesigned mobile app for automatic randomization once the research assistants input the participant’s unique study ID number. Due to the nature of the interventions, participants will not be blinded to their assigned study arm. Research assistants will also not be blinded, given their role in delivering the interventions. However, the outcome assessors and data analyst will remain blinded to the study arms.

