### Data Collection Procedures

Participants will be enrolled in the study and assigned a unique ID number, which will be used for randomization using the mobile app. Once the participant has been randomly assigned, baseline measurements and tracking information will be collected and recorded using the Open Data Kit (ODK) platform (Get ODK Inc) and directly uploaded to the server. Data will be collected on age, sex, occupation, date when identified as a person with presumed TB, distance to the health facility of enrollment, test method used (ie, sputum smear microscopy or Xpert MTB/RIF), and knowledge and perceptions about the disease and treatment. We will train outcome assessors to objectively conduct interviews and assess outcomes at follow-up. This approach will minimize any biases associated with the team administering the intervention.

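### Covariates for the effect models are to be picked by observed imbalance, from data collected after unblinded allocation that include test method; the set should be fixed in advance and test method kept out of it

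*Protocol article*

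**What the plan says.** The rule stands in the protocol article, Data Management and Analysis, Overview: "We will control for characteristics that are not balanced across the study arms in the fitted regression models". That section calls for descriptive statistics of participant characteristics by arm. It lists no covariates and does not say what counts as imbalance. It also makes intention to treat the primary approach.

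Data Collection Procedures describes the data from which covariates could come: "Once the participant has been randomly assigned, baseline measurements and tracking information will be collected and recorded". The list contains age, sex, occupation, date identified as having presumed TB, distance to the facility, and then "test method used (ie, sputum smear microscopy or Xpert MTB/RIF), and knowledge and perceptions about the disease and treatment".

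Table 1 (Trial End Points, Outcomes, and Timelines) shows the same order. Allocation is ticked under Screening. "Knowledge of and attitudes regarding TB" is ticked in the later Baseline column. The interventions start in the Day 0 column, and sputum submission is assessed at Day 30.

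On blinding, Randomization and Blinding says that "participants will not be blinded to their assigned study arm" and "Research assistants will also not be blinded, given their role in delivering the interventions", while "the outcome assessors and data analyst will remain blinded to the study arms".

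The primary outcome requires both an Xpert sputum sample and receipt of its result within 30 days. Its denominator is everyone recruited.

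**The concern.** Under randomisation, imbalance in a true baseline variable is chance. Selecting covariates on it ignores whether they predict completion of diagnosis. The model is not determined until the data are seen, different readings of imbalance give different adjusted estimates, and a strong predictor that happens to be balanced is omitted although adjusting for it would gain precision.

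Two items in this pool need more care, because they are recorded after an allocation that the participant and the interviewer both know.

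- **Test method.** If it means the test actually done, it has no value for people who were never tested, and it overlaps with the outcome. A participant tested only by smear microscopy cannot meet the primary endpoint. Adjusting for it would remove whatever part of the effect runs through sample submission. A complete-case fit would drop never-tested participants, against the intention-to-treat approach and the all-recruited denominator.
- **Knowledge and perceptions.** These are not part of the outcome. The weaker concern is that self-report may be coloured by knowing the arm, so that an imbalance need not be chance.

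**Working it through.** **1. How far the rule leaves the model open.** Data Collection Procedures lists eight items: age, sex, occupation, date identified, distance, test method, knowledge and perceptions. The protocol states no imbalance test. For illustration only, assume one 5% test per item and independent items. The chance that at least one is selected is 1 − 0.95^8 = 0.337, about 34%. This is the chance that some covariate enters the model. It is not a bias or an error rate.

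**2. Does selection by imbalance distort the test when covariates are true baseline variables?** This was simulated under no effect: 1,500 trials, 597 per arm (2389/4, a full arm under 2:2:2:1:1), 76% completion, seven prognostic baseline covariates, modified Poisson regression with robust standard errors, and covariates kept if unbalanced at p < 0.05. Rejection rates at the 5% level were:

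| Model | Rejection rate |
|---|---|
| Unadjusted | 5.3% |
| Adjusted for unbalanced covariates only | 5.1% |
| Adjusted for all seven | 6.2% |

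The Monte Carlo standard error is √(0.05 × 0.95/1500) = 0.56 percentage points. The rule shows no type I error cost here. The fixed set did no better on that score, so the case for it rests on prespecification, on precision and on the content of the set.

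**3. What happens if test method records the test done.** Inputs from Objectives and Hypothesis and from Sample Size Estimation: control loss 24%, and single-intervention loss 24% × (1 − 0.40) = 14.4%, which reproduces the stated figure. Taking loss as the complement of the primary outcome, completion is 76% versus 85.6%, and the risk ratio is 0.856/0.76 = 1.126.

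Participants without an Xpert sample all fail the outcome. With test method in the model, the risk ratio is estimated among those with Xpert done, whether the never-tested are dropped as missing or kept as their own category. Completion is submission × receipt given submission, so the conditional ratio is (0.856/s1)/(0.76/s0), where s0 and s1 are the proportions submitting in the control and intervention arms. The protocol gives neither, so both are assumptions. Feasibility requires s1 to be at least 0.856 and at most 1.

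| s0 | s1 | Receipt given submission, control | Receipt given submission, intervention | Conditional risk ratio |
|---|---|---|---|---|
| 0.85 | 0.957 | 0.894 | 0.894 | 1.00 (all of the effect through submission) |
| 0.85 | 0.90 | 0.894 | 0.951 | 1.064 |
| 0.85 | 0.856 | 0.894 | 1.000 | 1.118 (the most that can act through results) |
| 0.90 | 1.00 | 0.844 | 0.856 | 1.014 |
| 0.90 | 0.90 | 0.844 | 0.951 | 1.126 (all through results) |

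The adjusted ratio equals the total effect only when submission is the same in both arms. Otherwise it is attenuated, and it can reach 1.00.

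**4. Can the interventions shift knowledge?** Table 1 records knowledge at Baseline, before the Day 0 interventions, and the SMS text is neutral and omits the disease name. What remains is influence of known allocation on reporting, for which the protocol offers no figure.

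**The case against.** The strongest reply is that the protocol names no adjuster. The rule speaks only of characteristics, and the list in Data Collection Procedures is a collection list. Test method sits there beside age and sex, directly after the mention of baseline measurements. All participants are referred for Xpert, and sputum submission is a separate Day 30 assessment, so the item may simply record the test ordered. This stands in part. A reader might infer that the plan is to adjust for part of its own outcome, and the text does not support that. What it does show is a rule that fails to exclude such a variable and an item whose wording leaves its timing open.

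A reader might also infer that working interventions will make knowledge look unbalanced. The order in Table 1 speaks against this, as step 4 shows.

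Third, the data analyst and outcome assessors are blinded. This limits steering towards a favourable estimate. It does not fix the model in advance, and it does not stop a post-allocation variable from entering.

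Fourth, the simulation shows no inflation of type I error for true baseline covariates. This stands, and the 34% must not be read as a measure of harm.

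Finally, covariate lists are often left to the analysis plan. Here, however, the protocol states the selection rule itself, and that rule is what is criticised.

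**Conclusion.** The rule should be replaced. It selects covariates by observed imbalance without a set or criterion, so the adjusted estimate depends on the realised data and balanced prognostic variables are passed over. That much follows from the text alone. For true baseline variables such as age, sex and distance, which allocation cannot plausibly alter, the consequence is an undetermined model and forgone precision. Inflated false-positive risk was not shown.

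The larger consequence is conditional. If test method records the test done and enters the model, the risk ratio of 1.126 could be attenuated to as little as 1.00. With 85% of controls submitting a sample it could not exceed about 1.12. These figures rest on the assumed submission proportions, on the planned 24% and 14.4% losses, and on that reading of the item. Knowledge and perceptions are a lesser concern, limited to reporting under known allocation. Confidence is high on the selection rule and moderate on test method.

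**What to change.** Replace the sentence in the Overview with a covariate set fixed before the analyst is unblinded and used whatever the observed balance. Facility, age, sex and distance to the facility would serve as an example; all are already available, and the team may have better grounds for another list. Report baseline balance descriptively. State when test method is recorded and whether it means the test ordered or the test done. Exclude from the effect model test method, knowledge and perceptions, and any other variable that allocation or testing could affect.

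This needs no new data and leaves the sample size at 2389. The cost is that the team must commit to a list now. The Results section reports 2355 recruited and preliminary analyses under way, so a list fixed today may not precede all sight of the data. The date of fixing it, and what had been seen by then, should be reported.

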**Methods:**

This will be a 5-arm individual randomized controlled trial among persons with presumed TB aged 18 years or older who are referred for Xpert MTB/RIF testing. Participants will be randomly assigned (2:2:2:1:1) to (1) standard of care, (2) SMS reminders only, (3) telephone calls only, (4) SMS reminders and a transport incentive, and (5) telephone calls and a transport incentive. An estimated sample size of 2389 participants will be considered. The primary outcome will be completion of TB diagnosis, defined as submitting a sputum sample for Xpert MTB/RIF testing and receiving test results within 30 days of being identified as having presumptive TB. The secondary outcomes will include (1) TB treatment initiation, which will be defined as starting TB treatment within 30 days of being diagnosed; (2) median turnaround times for TB diagnosis and treatment initiation; and (3) acceptability and feasibility of the interventions. Participants will be followed for 30 days to check whether they have tested for TB and collected their results. Chi-square tests will be performed for categorical outcomes. Analysis will be by intention to treat. Modified Poisson regression models will be used to estimate the effects of the interventions on completion of TB diagnosis and treatment initiation.

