### Sample Size Estimation

An estimated sample size of 2389 participants was determined to achieve 80% power at a type I error of 5%, adjusted for multiple comparisons using the Bonferroni correction. Four comparisons were considered according to the study objectives; therefore, the adjusted level of significance is 1.25%, with a corresponding 2-tailed Z value of 2.238. We also adjusted for a 24% LTFU among patients with TB, based on findings from the formative study that informed the design of these interventions. We assumed a 40% reduction in LTFU based on previous similar studies [36,37] for comparisons between SOC and either SMS reminders alone or telephone calls alone, resulting in an assumed proportion of LTFU of 14.4% in both these groups. For comparisons between SOC and combined interventions (SMS reminders or telephone calls with a transport incentive), a 50% reduction will be considered clinically significant, given the expected higher impact of the incentive. The sample size has been further adjusted for clustering using a design effect of 1.5 to account for the clustering anticipated at the health facility level and a postenrollment attrition rate of 20%.

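### Abstract and Methods name different effect models with neither marked primary, and the facility design effect of 1.5 in the sample size matches neither the individual randomisation nor any stated analysis

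*Protocol article*

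**What the plan says.** **Effect model.** The Abstract, under Methods, states: "Modified Poisson regression models will be used to estimate the effects of the interventions on completion of TB diagnosis and treatment initiation". The Overview under Data Management and Analysis states: "Log-binomial regression models using generalized linear modeling will be applied to assess associations between each intervention and the outcomes". The Overview does not mention modified Poisson regression and the Abstract does not mention log-binomial regression. Nothing says that one is primary and the other a fallback or sensitivity analysis.

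**Covariates.** The Overview adds: "We will control for characteristics that are not balanced across the study arms in the fitted regression models". It also plans chi-square tests for categorical outcomes. It names no facility term, stratification, random effect or facility-clustered standard error.

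**Sample size.** Sample Size Estimation arrives at 2389 participants for 80% power, "using a design effect of 1.5 to account for the clustering anticipated at the health facility level", and allows for 20% attrition after enrolment. On the critical value it says "the adjusted level of significance is 1.25%, with a corresponding 2-tailed Z value of 2.238".

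**Design.** Trial Design describes a multicentre trial with individual randomisation. Study Setting lists six facilities. Randomization and Blinding gives a 2:2:2:1:1 ratio in permuted blocks of 8 and 16.

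**The concern.** There are two separate problems.

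First, two models are given for one estimate. Both target a risk ratio, and with arm alone they give practically the same answer. They part company once covariates enter. The log link does not keep a fitted risk below 1, and a log-binomial likelihood breaks down at that bound. Planned completion is 76% under standard of care and 85.6% to 88% under intervention, so there is little room. With no order of precedence, the choice between the models could be made after the results are known. Under Results, the article says that preliminary analyses are ongoing.

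Second, the sample size and the analysis rest on different pictures of the trial. A design effect for facility clustering belongs to a design in which whole facilities share an arm. Here each facility is expected to contribute to every arm, so a common facility effect largely cancels out of the arm contrasts. If facility matters, the natural place for it is the model, and the stated model does not have it. A reader cannot tell what power the stated analysis has.

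**Working it through.** **Inputs.** Loss before diagnosis is 24% under standard of care, 14.4% in single-intervention arms and 12% in combined arms (Objectives and Hypothesis). Ratio 2:2:2:1:1, Z = 2.238, 80% power, design effect 1.5, attrition 20%, N = 2389.

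**1. Reproduce 2389.** Pooled two-proportion formula, 24% against 14.4%, equal arms, mean proportion 0.192:

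n = [2.238 × √(2 × 0.192 × 0.808) + 0.8416 × √(0.24 × 0.76 + 0.144 × 0.856)]² / 0.096²
= (1.2466 + 0.4653)² / 0.009216 = 318.0 per full-size arm.

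Standard of care holds 2 of 8 shares, so the total is 4n = 1272.
- Attrition only: 1272 / 0.8 = 1590.
- With the design effect: 1590 × 1.5 = 2385 (2390 with Z = 2.2414).

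This matches 2389 only when the 1.5 is applied. About 795 participants are there because of it.

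**2. Power with and without the 1.5, at one critical value at a time.** After 20% attrition, standard of care has 2389 × 0.25 × 0.8 = 477.8 participants. Dividing by 1.5 gives an effective 318.5. A combined arm is half that size (mean proportion 0.20).

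Power = Φ[(difference − Z × s0) / s1], where s0 is the pooled and s1 the unpooled standard error.
- Single arm: s0 = √(0.310272/n), s1 = √(0.305664/n).
- Combined arm: s0 = √(0.48/n), s1 = √(0.3936/n), with n the standard-of-care number.

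Example, single arm with the factor, Z = 2.238: (0.096 − 2.238 × 0.03121) / 0.03098 = 0.844, so power is 80.1%.

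| Z | Design effect | Single | Combined |
|---|---|---|---|
| 2.238 (protocol) | 1.5 | 80.1% | 82.7% |
| 2.238 (protocol) | none | 93.8% | 95.6% |
| 2.498 (two-sided 1.25%) | 1.5 | 72.0% | 74.4% |
| 2.498 (two-sided 1.25%) | none | 90.0% | 92.3% |

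No facility term enters this table. Differences between rows with the same Z come wholly from the 1.5.

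**3. Effect of leaving facility out.** Simulation with six facilities, individual allocation, about 478 per full-size arm, nominal alpha 0.0125 and an assumed facility intraclass correlation from 0 to 0.10:
- ignoring facility: type I error 0.010 to 0.013, power 0.88 to 0.90;
- stratifying by facility: type I error 0.012 to 0.014, power 0.89 to 0.90.

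**4. Log-binomial stability.** Simulations used N = 2355, the planned completion rates and six facilities.
- Arm only, or arm plus facility: no failures in 100 data sets per setting.
- Adding age, distance and sex with assumed effects: the fit did not converge, stopped with an error or gave fitted risks of about 1 or more in anything from 7% to 100% of data sets, rising with the assumed effects.
- Poisson regression failed in 0%.

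**The case against.** **The model conflict is slight.** Both models estimate a risk ratio, modified Poisson is already named in the Abstract, and log-binomial fits with arm or arm plus facility did not fail. All of that stands. The failure rates rest on three covariates with assumed effects, whereas the Overview adjusts only for characteristics found unbalanced. One cannot infer that the planned model will fail, only that it is exposed to failure when adjustment is needed. The contradiction between Abstract and Methods remains.

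**The facility term is a detail for the full analysis plan.** Centre terms and the type of standard error are often left there, and such a plan may well include them. The absence alone would not be a point. What the article does fix is a facility allowance of 1.5 that individual randomisation does not call for and that no analysis it describes uses.

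**The inflation errs on the safe side.** It does: it makes the trial larger than this design needs. Recruitment stood at 2355, so the number enrolled is no longer in question.

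**Stronger readings to avoid.** A reader might infer that omitting facility makes the tests anti-conservative or leaves the trial underpowered. The simulation shows neither. A reader might set 90% beside 72% and credit the facility term with 18 points; the whole gap comes from dropping the 1.5. The 72% also requires replacing the protocol's Z of 2.238 with 2.498, which is a separate question. Finally, the article says only that clustering by facility is anticipated, not that facility is the main driver of completion.

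**Conclusion.** The point holds in two limited parts.

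The article names two models for one set of effects and ranks neither. This follows from the text and needs no assumption. Modified Poisson is the numerically safer choice at 76% to 88% completion with covariate adjustment; the size of that advantage depends on unknown covariate effects.

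The 1.5 factor accounts for about 795 of the 2389 participants, but cluster-type inflation is not needed here and no stated analysis uses facility. The consequence is an unclear power statement, not a biased or invalid test. Adding facility gains about one point of power at most, over an assumed intraclass correlation of 0 to 0.10 and balanced allocation within facilities. The power figures assume the protocol's loss rates and the full 20% attrition.

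This should be corrected, but it does not undermine the trial.

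**What to change.** **Abstract (Methods) and Data Management and Analysis (Overview).** Name the same primary analysis in both: modified Poisson regression (log link, robust standard errors) on all randomised participants, with arm and the six facilities as fixed effects, and four contrasts with standard of care. Do not cluster the standard errors by facility, because six clusters are too few for that to be reliable. If log-binomial is kept, label it a sensitivity analysis.

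**Sample Size Estimation.** Describe the 1.5 as a conservative margin. Give power with and without it at the same critical value: about 80%/83% and 94%/96% (single/combined arms) at Z = 2.238, or about 72%/74% and 90%/92% at 2.498. Do not attribute the difference to the facility term.

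**Cost.** Wording, ideally settled before any comparison by arm is seen, and five extra model parameters. Facility is already known for every participant, and no change in N is needed.
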